## 1.0 General Information

### 1.1 Protocol Title

Comparison of the performance of the Epi proColon - test and Fecal Immunochemical Testing (FIT) post colonoscopy in subjects with Colorectal Cancer (CRC) and pre colonoscopy in subjects from guideline-eligible screening population.

### 1.2 Short Title

Head to Head Study Epi proColon and FIT

### 1.3 Protocol Number

SPR 00XX

### 1.5 Name and Title of the Person(s) Authorized to Sign Protocol and Protocol Amendments for the Sponsor

Same as approver list on front page.

### 1.7 Name and Title of the Monitors

In addition to the above named Sponsor Representatives, other authorized and GCP trained personnel from Epigenomics or designee will act as Study Monitors.

## 2.0 Background Information

### 2.1 Rationale for the Study

The study will be conducted with the aim to show non-inferiority in the clinical performance of the investigational Epi proColon assay to FIT - OC FIT-CHEK® (Polymedco) - using matched blood and stool specimens from screening-guideline eligible subjects.

### 2.2 Technical Data to Date

Epigenomics has identified methylated gene regions that are specific for colorectal cancer (CRC). Through Epigenomics' marker discovery and validation process, DNA methylation of a region of the Septin9 gene was identified as a robust biomarker for detection of CRC. Epigenomics developed a blood test for CRC based on the detection of the Septin9 biomarker called Epi *proColon* Early Detection Assay, available as a CE-

marked kit in Europe since October 2009. According to the results of the performance evaluation study, the first generation product detected approximately 70 % of the CRC cases with a specificity close to 90 %. In a CRC screening cohort (PRESEPT), the Septin9 biomarker assay detected 67 % of CRC cases with a specificity of 89 %. A second generation Septin9 biomarker assay with improved clinical performance characteristics has been developed. Epigenomics is performing the current study to directly compare the second generation Epi *proColon* 2.0 assay with the current non-invasive standard for colorectal screening, FIT, in order to provide supporting data for safety and effectiveness of the Epi *proColon* 2.0 investigational device for its proposed intended use.

### 2.3 Study Summary

This study is designed to prospectively collect matched blood and stool specimens and clinical data from screening guideline-eligible subjects found to have invasive colorectal cancer (CRC) at colonoscopy, i.e. AJCC/UICC stages I, II, III, and IV, with collection of specimens and testing after colonoscopy and from screening guideline-eligible subjects with blood and stool specimens collected before colonoscopy.

## 3.0 Trial Objectives and Purpose

### 3.1 Primary Objective of the Study

The primary objective of the investigation is to show that the clinical performance in terms of test positivities of the investigational Epi *proColon* test is non-inferior to OC FIT-CHEK®, (Polymedco), a commonly used and commercially available (in the United States) fecal immunochemical test (FIT) used for the detection of colorectal cancer.

## 4.0 Trial design

### 4.1 General Design

The study is designed as a prospective case-control clinical investigation involving up to 40 active study sites in the United States and in Europe. European enrollment will be limited to 20% of the subjects. Subjects interested in participation and who provide written informed consent will be enrolled in the study provided inclusion criteria are met. Eligible, consented CRC subjects and controls will have up to 40 ml of blood drawn and will provide the amount of stool required per manufacturer's instructions of the OC FIT-CHEK® test. DNA obtained from plasma will be bisulfite-converted and assessed for presence of methylated Septin 9 following the instructions for use provided with the investigational Epi *proColon* test. Stool samples will be processed in accordance with the manufacturer's instructions.

### 4.2 Investigational Plan

The clinical performance of the investigational Epi *proColon* test will be compared to that of OC FIT-CHEK®.

### 4.3 Sample Number and Amounts

This study aims to enroll two different subsets of subjects which are described below. In order to include into the study the following numbers of fully compliant subjects, the estimate is that we need to recruit 200 subjects per group (assumes 50% attrition rate, therefore 100 evaluable per group.)

Group A: 100 subjects between age 50 and 84 having CRC, consented and specimens collected and tested after colonoscopy

Group B: 100 subjects between age 50 and 84, consented and tested before colonoscopy and bowel preparation. It is planned to obtain both blood and stool samples from all subjects enrolled into the study. Both Group A and B must include 100 subjects each who have provided both a blood sample and stool sample for FIT. The study will be continued until these quotas will have been reached. Enrolled subjects not providing both samples according to this protocol will be considered screen failures and will not be evaluated.

Enrollment will be conducted so that ages of subjects in the two groups are not disparate. These sample numbers are considered appropriate for the calculations mentioned in the following paragraph.

### 4.4 Randomization and Blinding

Randomization will not occur: Only subjects who provide both types of samples will be evaluated. The laboratories performing the tests will be blinded with regard to the subject's clinical diagnosis.

## 5.0 Selection and Withdrawal of Subjects

Group A CRC subjects participating in the study will be selected and sourced from an average-risk, screening guideline eligible population who have undergone colonoscopy and who have been diagnosed with colorectal cancer. Group B subjects will be enrolled from an average-risk, symptom-free population who are scheduled to have colonoscopy.

### 5.1 Inclusion Criteria

#### Group A

- 1) Willing and able to sign an IC and adhere to study requirements.
- 2) Both genders eligible.
- 3) 50 – 84 years of age at blood & stool sampling.
- 4) Colonoscopic diagnosis of colorectal carcinoma (CRC).\*
- 5) Colonoscopy within 6 months before inclusion into the study, i.e. latest colonoscopy must be in the past 6 months.
- 6) Blood & stool sampling a minimum of 10 days after colonoscopy and before resection surgery.

*\* = strong clinical suspicion of colorectal carcinoma is also acceptable for subject enrollment; Case must have a confirmed diagnosis after surgery of CRC and be accompanied by a complete final pathology report.*

**Group B**

- 1) Willing and able to sign an IC and adhere to study requirements.
- 2) Both genders eligible.
- 3) 50 – 84 years of age at blood and stool sampling.

**5.2 Exclusion Criteria****Group A Only:**

- 1) Subject with curative biopsy during colonoscopy.

**Group A and B:**

- 1) Previous personal history of CRC or previous colonoscopy resulting in a recommendation to repeat colonoscopy at an interval less than ten years (high risk population).
- 2) Neoadjuvant treatment
- 3) Familial risk for colorectal cancer (2 or more 1st degree relatives with CRC; 1 or more 1st degree relative(s) < 50 years with CRC; known HNPCC or FAP).
- 4) History of inflammatory bowel disease.
- 5) Acute or chronic gastritis.
- 6) Current diagnosis of any other cancer than CRC.
- 7) Overt rectal bleeding or bleeding hemorrhoids.
- 8) Known infection with HIV, HBV or HCV.
- 9) Subject concurrently receiving intravenous fluid at the time of the specimen collection.

**6.0 Treatment of Subjects****6.1 Blood Specimen and Sampling Requirements**

Plasma specimens will be prepared according to the Instructions for Use of the Epi proColon investigational device (IFU 0008) with the exception that multiple blood tubes will be drawn and multiple aliquots of plasma prepared for each subject. Consented subjects will provide up to 40 ml of blood.

**6.2 Blood Collection (at the investigational site)**

Vacutainer® EDTA Tube (Becton Dickinson, catalogue no. 366643) 10 ml tube will be used for drawing blood. Whole blood samples must not be frozen.

Processing of whole blood must begin within four hours of blood collection. After initial collection of plasma from centrifuged whole blood or after a second centrifugation of collected plasma, specimen can be stored at 2 to 8°C for up to 72 hours prior to further processing or freezing.

### 6.3 Stool Specimen and Sampling Requirements

Stool samples for FIT will be collected and tested according to the manufacturer's instructions for use for OC FIT-CHEK® (PolyMedco).

### 6.4 Stool Samples collection

The subjects will be instructed, according to manufacturer's instructions, to collect the stool sample as follows:

- 1) place the supplied collection paper inside toilet bowl on top of water,
- 2) deposit stool sample on top of collection paper,
- 3) collect test sample from stool sample before paper sinks and stool sample touches water,
- 4) fill in required information (name, age, gender, date) on sampling bottle,
- 5) open sampling bottle,
- 6) scrape the surface of the fecal sample with the sample probe,
- 7) cover the grooved portion of the sample probe completely with stool sample,
- 8) close sampling bottle by inserting the sample probe and snap cap on tightly,
- 9) do not reopen sampling bottle,
- 10) keep sampling bottle between 2 and 30°C,
- 11) put the sample in the envelope and return it to the laboratory the same day.

The study nurse will follow-up with the subject by phone to remind her/him to provide the stool samples.

### 6.5 Plasma Specimen Preparation (at the laboratory)

- Disable the brake function in the centrifuge to prevent disruption of the cell layer.
- Centrifuge the blood in Vacutainer® (or S-Monovette tubes) for 12 min at  $1350 \pm 150$  rcf. If centrifuge uses RPM (revolutions per minute), refer to the centrifuge user manual for a conversion table.
- Remove Vacutainer® from centrifuge. Discard the sample if haemolysis (bright red plasma) is observed. In this case a new blood sample must be taken.

- Use a Pasteur single-use pipette to transfer plasma from the collection tube to a 15 ml polypropylene centrifuge tube with conical bottom.
- Centrifuge plasma in the 15 ml centrifuge tube for 12 min at  $1350 \pm 150$  rcf.
- Using a new bulb pipette, transfer 4.0 ml plasma into labelled cryovials or centrifuge tubes.

#### **6.5.1 Blood Specimen Inclusion Criteria**

- At least 12 ml plasma sample per patient.
- Plasma collected, processed, shipped and stored according to provided Instructions for Specimen Processing.
- All CRFs complete including complete staging information for colorectal cancer cases.

#### **6.5.2 Blood Specimen Exclusion Criteria**

- Specimen thawed after initial freezing (except at testing).
- Gross hemolysis of plasma specimen.

#### **6.6 Treatments authorized/not permitted before and/or during the specimen collection**

Processed blood specimens will be stored at the site or the Laboratory, which processed the plasma until bulk shipment as requested by the Sponsor. Packaging of blood specimens and shipping will be performed according to Specimen Shipment Instructions using a courier specialized in shipping frozen specimen for diagnostic use. Temperature may be monitored during shipment with single use temperature monitoring devices provided by the Sponsor indicating a temperature above  $-1^{\circ}\text{C}$ .

Specimens will be stored in a  $-70^{\circ}\text{C}$  (or colder) freezer at Epigenomics or designee until they are analyzed by Epigenomics or shipped to authorized laboratories.

#### **6.7 Treatment of Plasma Specimens at Epigenomics or at an External Laboratory**

Upon arrival of the specimens at Epigenomics' or designee's facilities, Epigenomics or designee will perform the following quality control on the specimens:

- Specimen is frozen upon receipt
- Accurate identification and labeling of specimen tubes
- Minimum of 12 ml plasma volume
- No evidence of gross hemolysis or turbidity

Only plasma specimens that have passed this quality control will be included in the analysis. The result of these quality controls will be documented at Epigenomics or designee during the check-in process, and communicated to the Provider.

All experiments may be conducted in cooperation with commercial partners of Epigenomics either in the facilities of Epigenomics or at the facilities of the respective authorized partner. Data will be shared with Epigenomics' partners as it relates to the study herein defined.

Surplus sample material will remain at Epigenomics or designee. Other molecular analysis may be performed whether or not contemplated by this Study Protocol. No genetic profiling is foreseen in the context of the investigation.

## **6.8 C-FIT CHEK Testing Procedures**

Testing will take place in the central laboratories (one in the US, one in Europe) using the manufacturer approved automated systems OC-Auto Micro 80 or OC-Sensor Diana at an 100 ng/ml cut-off. The central laboratories will also provide the raw QUANTITATIVE data on request for further analysis. The laboratory doing the testing will report the result directly into the specific section of the CRF without having access to other information contained in the CRF. There are no medicinal or dietary restrictions for the use of OC-FITCHEK.

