### 12.2 Case Report Forms

Paper CRFs or remote electronic data capture (EDC) will be the primary data collection instrument(s) for the study. All data requested must be correct, accurate, legible and complete. CRFs and EDC systems should be filled in by the Principal Investigator for the institution, or his/her designee. Any change or correction should be dated, initialed (signed), and explained (if necessary) by the person responsible for making the change.

Changes to paper records should not obscure the original entry (i.e. an audit trail is maintained). The correct way to make a correction is to cross out the original entry with a single line. No correction fluid may be used. This allows the original entry to remain legible. Example: "cold" sinus infection. The wrong data entry "cold" is crossed out and the correct response, "sinus infection" is written beside the entry. Clearly initial and date beside the lined out item.

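### Only the laboratories are blinded: nothing keeps the Group B FIT result from those who assign CRC/NED status, so the reference standard may be read with the comparator result known

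*Protocol*

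**What the plan says.** Section 4.4 contains the only general blinding rule: "The laboratories performing the tests will be blinded with regard to the subject's clinical diagnosis".

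Section 6.8 governs FIT reporting: "The laboratory doing the testing will report the result directly into the specific section of the CRF", and the laboratory does so "without having access to other information contained in the CRF". This restriction also binds the laboratory alone.

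On timing, Section 4.3 describes Group B as "consented and tested before colonoscopy and bowel preparation". Section 2.3 refers to "screening guideline-eligible subjects with blood and stool specimens collected before colonoscopy". Section 6.4 tells the subject to "put the sample in the envelope and return it to the laboratory the same day".

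On the form, Section 12.2 states: "CRFs and EDC systems should be filled in by the Principal Investigator for the institution, or his/her designee". Section 10.1 lists colonoscopy and histology information among the contents of the CRF. Sections 12.2 and 12.9 allow either paper or electronic capture.

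On the other test, Section 6.6 has processed blood specimens stored at the site or at the laboratory "which processed the plasma until bulk shipment as requested by the Sponsor".

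Section 9.1 makes medical diagnosis/colonoscopy the reference standard and uses it to fix the NED count, which is the specificity denominator for both tests.

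**The concern.** In a paired accuracy study the reference standard should be read without knowledge of either test. Here the index tests are protected from the diagnosis, but the diagnosis is not protected from the tests. A positive FIT known to the endoscopist or pathologist could prompt a closer examination. If that turns up lesions that remove the subject from NED, a FIT false positive disappears from the specificity calculation. The Epi proColon result is less likely to be available at that time, so the effect would tend to favour the comparator.

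The quantities at stake are the FIT specificity reported under Sections 7.0 and 9.1, the paired specificity difference, and the superiority analysis in Section 9.4. Group A sensitivity is largely outside the problem: Section 5.1 places sampling at least 10 days after colonoscopy, so FIT cannot influence that examination. Cases enrolled on clinical suspicion do have their diagnosis confirmed after sampling, but by surgery and a final pathology report.

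This is a rule of conduct rather than of analysis. A statistical analysis plan would not be expected to supply it, and could not repair an examination already made with FIT known.

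**Working it through.** **Step 1: can the result reach the reference assessor?** The plan gives no figure on this point, so the provisions are set side by side.

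- Can a FIT result exist before the Group B colonoscopy? Yes. Section 4.3 has Group B tested before colonoscopy, and Section 6.4 has stool returned the same day. No reporting turnaround is stated, so the result can exist by then but need not.
- Where does it go? Into a section of the CRF (6.8), a form that the site fills in (10.1, 12.2) and that also holds the reference data (10.1).
- Does any rule close that section to the site? No. Sections 4.4 and 6.8 restrict only the laboratories. With paper CRFs permitted, closure cannot be presumed from a system setting.
- Does any rule blind the endoscopist, the pathologist or the staff recording CRC/NED status? None.

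**Step 2: how large could the effect be?** Let *f* be the FIT false-positive rate among true NED subjects, and *r* the share of those false positives moved out of NED because FIT was known. The protocol gives neither. Both are assumptions: *f* = 5%, 8%, 11% and *r* = 10%, 20%, 30%.

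Apparent FIT specificity = (1 − f) / (1 − f·r)

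| f | true | r = 10% | r = 20% | r = 30% |
|---|---|---|---|---|
| 0.05 | 0.950 | 0.955 (+0.5) | 0.960 (+1.0) | 0.964 (+1.4) |
| 0.08 | 0.920 | 0.927 (+0.7) | 0.935 (+1.5) | 0.943 (+2.3) |
| 0.11 | 0.890 | 0.900 (+1.0) | 0.910 (+2.0) | 0.920 (+3.0) |

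Gains are in percentage points. Corner cases: 0.95/0.995 = 0.955 and 0.89/0.967 = 0.920. In 100 NED subjects the number reclassified is 100·f·r, that is 0.5 to 3.3 people. The absolute ceiling is r = 100%, where apparent specificity is 1 and the gain equals *f*: 5 to 11 points on these assumptions, still below the 20-point margin.

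**Step 3: what happens to Epi proColon specificity?** Let *e* be its false-positive rate and *q* the share of FIT false positives that are also Epi proColon positive.

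Apparent Epi proColon specificity = (1 − e − f·r·(1 − q)) / (1 − f·r)

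If the two tests' false positives are independent, q = e and this equals 1 − e: no change, so the whole FIT gain passes into the paired difference. At the other extreme, with e = f and q = 1, it equals the FIT expression and the paired difference does not move. The gains in the table are therefore the shift in the difference under independence, and less if false positives overlap.

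**Step 4: scale.** At a true difference of zero, the standard error of the paired difference is √(discordance/n). With n = 100 and an assumed discordance of 10% to 20%, √(0.10/100) = 3.2 points and √(0.20/100) = 4.5 points. Even the 3.0-point corner lies below one standard error.

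**The case against.** The strongest reply has four parts.

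First, site access is inferred. Section 6.8 describes a sectioned form, and Sections 10.1 and 12.2 say who completes the CRF, not who may read which part and when. This stands: a reader might infer that the site sees the FIT result before colonoscopy, and the protocol does not say so. What remains is that nothing prevents it. Section 12.6 has deviation reports filed with the subjects' CRFs in the Regulatory Binder, which Section 11.5 describes as the site's.

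Second, if testing before colonoscopy in Section 4.3 is taken literally it covers both tests, and the asymmetry between FIT and Epi proColon goes. If it is taken loosely to mean collection, it does not establish that a FIT result exists by then. This also stands in part. The asymmetry rests on bulk shipment of plasma against same-day return of stool, which makes it likely but not certain. If both results were available early, the one-way direction would weaken, but the reference would still be unblinded.

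Third, reclassification requires that the extra lesions disqualify a subject from NED. The protocol does not say whether polyps or adenomas do. If only cancer counts, 10-30% reclassification would be implausibly high.

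Fourth, a bias against the investigational test cannot produce a false non-inferiority finding on specificity. That is correct.

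**Conclusion.** The point holds as a gap in blinding: the protocol sets a one-way rule that permits the reference standard to be read with the comparator result known. It should be corrected, but it is not fatal to the primary comparison.

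The size, about 0.5 to 3.0 points of apparent FIT specificity, depends wholly on the assumed false-positive and reclassification rates, on FIT being known when Epi proColon is not, on extra lesions removing subjects from NED, and (for the paired difference) on little overlap of false positives.

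Two stronger readings are tempting and are not supported. One is that the bias always runs the same way. The documents leave open both the timing of Epi proColon results and the lesions that end NED status, so the direction is a tendency. The other is that the 0.20-margin conclusion is in danger. The shift is small against that margin and makes non-inferiority harder, not easier, to show.

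The remaining harm is to the FIT specificity reported in its own right and to the superiority analysis of Section 9.4, where no margin absorbs a shift and the specificity comparison would be tilted against Epi proColon.

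**What to change.** In Section 4.4, add that the endoscopist, the pathologist and the staff who record CRC/NED status are blinded to both FIT and Epi proColon results.

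In Section 6.8, replace direct entry in the shared CRF by transfer to data management, or by a separate laboratory form or EDC section closed to the site. The separate form also covers sites that use paper. State that results are released only after the colonoscopy and pathology entries are locked.

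Add a defined release point for subjects who leave without colonoscopy. Section 5.0 says only that Group B subjects are scheduled for the examination, and Section 9.2 assumes 50% attrition, so such subjects may occur. The sponsor and investigators should set that point.

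The cost is a few sentences, an access setting or a separate form, a small data-handling step, and later availability of results to the sites. Enrolment and sample size are unaffected.

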## **7.0 Assessment of Efficacy**

The FIT and Epi proColon assessments will be compared to medical diagnosis/colonoscopy for determination of sensitivity and specificity and reported along with 95% confidence intervals for the point estimates. Positive and negative percent agreement between FIT assessment and Epi proColon assessments will also be provided with corresponding 95% confidence intervals.

